### Type and design of the study

4.1

The present study is a randomized controlled experiment in N = 100 SUD- inpatients during a therapeutic community treatment with one intervention group that will receive an additional 6-week smoking cessation intervention and one control group that will receive treatment as usual. The study design consists of a 2 x 2 mixed subject design with repeated measures for the biological analyses and a 2 x 3 mixed subject design with repeated measures for the psychobehavioural analyses (see **Table 1**). In both groups, an examination of metabolic and gut microbial profiles, as well as psychological variables, will take place. Biological parameters will be ascertained from blood and stool specimens for nuclear magnetic resonance (NMR) spectroscopy metabolomic analyses and from stool specimens for 16s-mRNA (hypervariable V3-V4 regions) sequencing and subsequent gut microbial profiling. Psychobehavioural and biological data will be collected pre & post smoking cessation, and additionally, there will be a follow-up measurement of the psychobehavioural variables 3 months upon completion of the study (see **Figure 3**: Consort Flow Chart for further illustration).

**Table 1 T1:** Overview of the statistical design.

Study group	Pre- intervention baseline	Post- intervention after 6 weeks	Follow- up after 3 months
Intervention Group (N = 50)	Psychobehavioural Data	Psychobehavioural Data	Psychobehavioural Data
	Metabolic/Microbial Data	Metabolic/Microbial Data	
Control Group (N = 50)	Psychobehavioural Data	Psychobehavioural Data	Psychobehavioural Data
	Metabolic/Microbial Data	Metabolic/Microbial Data	

green cells: biological data; light brown cells: self-report data.

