#### Statistical analyses of psychological variables

4.7.4

The statistical analyses will be performed in SPSS version 29 (IBM) for general procedures, while specific regression models are handled in R (R core team (121)). For example, t-tests will be carried out for independent and paired comparisons of means between and within groups at different times, respectively, assuming that the continuous data are normally distributed. Chi-square and Fisher’s exact tests, the latter in cases of smaller sample sizes, will be conducted in order to test the associations between categorical variables. The Friedman test shall be used in analyzing non-parametric repeated measures. The main effects of the intervention, time effects, and group x time interaction will be tested using a 2 × 3 two-way repeated measures ANOVA design (group x time), using the Greenhouse-Geisser correction in cases when the sphericity assumption will be violated. The level of significance will be α = 0.05, two-tailed, using Bonferroni adjustment for multiple comparisons. In addition, a repeated measures proportional odds logistic regression model using a generalized estimating equation (GEE) will be applied, assessing the intervention’s effect on CPD treated as an ordinal variable. The GEE model, computed in R using the `repolr` package (122), will contain robust variance estimators that take into account within-subject correlations (**Table 2**).

**Table 2 T2:** Summary of statistical methods and outcomes.

Outcome variable	Domain	Statistical method	Software
Self-efficacy, craving, psychiatric scores	Psychobehavioural	Repeated measures ANOVA, t-tests, Friedman test	SPSS
Cigarettes per day (ordinal)	Psychobehavioural	GEE (Proportional odds model)	R (repolr)
Bacterial diversity indices	Microbiome	Kruskal-Wallis, ANOSIM, db-RDA	R, QIIME
Taxonomic composition	Microbiome	MaAsLin2, ANCOM, LEfSe	QIIME2, R
Metabolite concentrations	Metabolic	PCA, O-PLS-DA, correlation analyses	NMR tools, R
Cross-domain associations	Combined (exploratory)	Correlation and regression	R

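### The scale scores would be better served by a baseline-adjusted mixed model than by a 2 × 3 repeated-measures ANOVA, and the Friedman test cannot compare the arms

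*Protocol article*

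**What the plan says.** Section 4.1 sets out "a 2 x 3 mixed subject design with repeated measures for the psychobehavioural analyses": baseline, 6 weeks and a 3-month follow-up. Section 4.7.4 tests the main effects and the group × time interaction in a 2 × 3 "two-way repeated measures ANOVA design (group x time), using the Greenhouse-Geisser correction in cases when the sphericity assumption will be violated". The same section adds that "t-tests will be carried out for independent and paired comparisons of means between and within groups at different times", on the assumption that continuous data are normally distributed, and that "The Friedman test shall be used in analyzing non-parametric repeated measures".

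Table 2 assigns "Repeated measures ANOVA, t-tests, Friedman test" to self-efficacy, craving and psychiatric scores, with SPSS as the software. Cigarettes per day is handled separately by a proportional-odds GEE in R, "assessing the intervention’s effect on CPD treated as an ordinal variable".

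Section 4.7.1 gives the planning values: correlation 0.5 between measurements, about 10% attrition and a total of 100 participants. Linear mixed models (lme4) appear in section 4.7.2, but only for nutrition adjustment of candidate biomarkers.

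**The concern.** Three features of the stated method need attention.

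- **Missing waves.** The usual SPSS repeated-measures ANOVA needs a complete row per participant. Someone seen at baseline and 6 weeks but not at 3 months contributes nothing to it, not even to its 6-week contrast.
- **Baseline.** It enters as one of three outcome levels. In a randomised trial it does more work as a covariate, because the arms differ at baseline only by chance.
- **Friedman.** It ranks the waves within each participant and asks whether the waves differ. It has no term for arm or for arm × time, so it cannot answer the trial's question for a non-normal scale.

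Self-efficacy and craving are the outcomes in the headline hypothesis, and section 2.1.1 makes group differences at 3-month follow-up a stated aim. Precision and a usable between-arm test therefore matter most here.

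**Working it through.** **Inputs from the protocol.** Section 4.7.1: f = 0.25, power 0.90, α = 0.05, correlation r = 0.5, about 10% attrition, N = 100, pilot self-efficacy effect d ≈ 0.70. Section 4.7.4: two-sided α = 0.05. **Assumptions of this check:** equal variances at each wave, true effects of 0.5 and 0.6 SD beside the pilot's 0.7 SD, and no Bonferroni adjustment.

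**1. The plan's own sample size.** For the two-wave interaction, λ = f² × N × m / (1 − r).
- N = 46 in total: λ = 0.0625 × 46 × 2 / 0.5 = 11.5; critical F(1, 44) = 4.06; power 0.91.
- N = 92 (46 per group): λ = 23.0; critical F(1, 90) = 3.95; power 0.997.

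The printed critical F of 4.06 fits 46 in total, not 46 per group. That is a separate matter. What counts here is the effect implied by f = 0.25. In a 2 × 2 layout each cell's interaction term is a quarter of the arm difference in change, so f = 0.25 means a difference of 4 × 0.25 = 1.0 SD. At that size, power stays above 0.99 with 90 participants, and the choice of method hardly affects it.

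**2. Baseline as outcome level or as covariate.** Per-participant variance of a two-wave contrast, in SD² units:
- change score: 2(1 − r) = 2 × 0.5 = 1.00
- baseline as covariate: 1 − r² = 1 − 0.25 = 0.75
- ratio: (1 + r)/2 = 0.75, a 25% reduction (35% at r = 0.3, 15% at r = 0.7)

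The equivalent gain in sample size is 1/0.75 = 1.33.

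Power by noncentral t, with 100 less 10% leaving 45 per arm, and noncentrality d / √(2 × variance / 45):

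| True effect | Change contrast | Baseline-adjusted |
|---|---|---|
| 0.5 SD | 0.65 | 0.77 |
| 0.6 SD | 0.80 | 0.90 |
| 0.7 SD (pilot) | 0.91 | 0.97 |

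This is a two-wave comparison. It shows the direction and rough size of the gain, not the exact power of the three-wave omnibus test.

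**3. Missing waves.** If the whole 10% is lost between 6 weeks and 3 months, the ANOVA's 6-week contrast uses 45 per arm although 50 per arm were measured. At 0.5 SD, recovering them lifts power for the change contrast from 0.65 to 0.70. Adding baseline adjustment takes it to 0.82. If the losses occur before 6 weeks, no 6-week data exist to recover, and only the gain in step 2 remains.

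**4. Friedman.** Simulated with 90 participants pooled over arms, three waves and r = 0.5:
- both arms improve by 0.5 SD, so there is no arm effect: rejects in about 99% of runs
- arms move 0.4 SD in opposite directions, an arm difference of 0.8 SD: rejects in about 4% of runs, no more than the nominal 5%

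The test responds to time and not to treatment.

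**5. What remains for a non-normal scale.** Section 4.7.4 ties the t-tests to normality. Kruskal-Wallis is named only for bacterial diversity indices (Table 2 and section 4.7.5). The ordinal GEE is named only for cigarettes per day. No between-arm method suited to a non-normal scale score is left.

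**The case against.** The case on the other side is substantial, and much of it stands.

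- **The arms are compared.** The ANOVA is stated without condition, and independent t-tests between arms are planned at the different times. A reader might infer that skewed outcomes fall back on within-arm paired tests, or that the group difference goes untested. The text supports neither. It never says that Friedman replaces the ANOVA, and Table 2 lists the methods side by side. What survives is narrower: no between-arm test suited to non-normality is named.
- **The 6-week data are not lost everywhere.** The 6-week independent t-test would keep a participant who is missing at 3 months. The loss is confined to the ANOVA.
- **Complete-case analysis is not written down.** It follows from how the named procedure works. The statistical analysis plan is not shown and may address missing data.
- **Biased dropout is not established.** A reader might infer that attrition will be informative or unequal by arm and will invalidate the test. The protocol gives only a figure of about 10%. Under one assumed mechanism (dropout depending on the 6-week score in the intervention arm only), simulated type I error was about 0.065 at a nominal 10% loss. The mechanism is hypothetical.
- **Baseline as an outcome level is not an error.** The interaction test is valid under randomisation. At the pilot effect of 0.7 SD it already reaches 0.91, above the 0.90 target.

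**Conclusion.** The point holds as an improvement in efficiency and robustness, together with a correction of Friedman's role. It does not show that the planned analysis is invalid. It covers self-efficacy, craving and psychiatric scores only.

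Baseline adjustment cuts the variance of a two-wave contrast by 25% at r = 0.5. The gain in power is about 0.12 at 0.5 SD, 0.10 at 0.6 SD and 0.06 at 0.7 SD with 45 per arm. It is negligible at the roughly 1.0 SD difference implied by f = 0.25. The gain from retaining partial follow-up depends on when participants are lost; at the expected 10% it is modest.

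The Friedman point rests on the construction of the test and needs no assumption about dropout or effect size. How often it would matter depends on how skewed the scales turn out to be, which the protocol does not say.

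**What to change.** Make the main analysis of each scale score a linear mixed model on the 6-week and 3-month values, with arm, time, arm × time, baseline and baseline × time. Include every randomised participant with any follow-up value, and report the arm difference with its confidence interval at each time.

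For non-normal scales, use the same model with robust or bootstrap standard errors, or an ordinal model, in place of Friedman. Keep within-arm paired tests as descriptive.

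The cost is a change of wording in section 4.7.4 and Table 2, plus somewhat more analysis work. No new data are needed. R is already in use, although lme4 is currently planned only for the nutrition-adjusted biomarker models. The model assumes that missing values are missing at random, which should be stated. The change should be fixed before outcome data by arm are seen.

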A-priori sample size calculations were performed with G-Power (108) (version 3.1.9.6), for a mixed-design ANOVA with one interaction between group (2 groups) and assessments (2 repeated measurements). Considering the effects mentioned above, the mixed-design ANOVA was set rather conservatively for a medium effect size (Cohen’s F = 0.25), a statistical Power (1-β) of 0.9, a α of 0.05, an intra-correlation coefficient of 0.5 and nonsphericity correction of 1, resulting in a minimum sample size of 46 subjects per group, and a critical F = 4.06. Adjusting for expected attrition of about 10%, a total sample size of size of 100 is set. The many (mostly biological) variables measured in this study will expectably require statistical corrections; this will also be compensated by statistical methods exceeding classical linear approaches, namely machine learning feature detection and modelling methods (109).

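### Section 4.7.4 fixes single-step Bonferroni for the psychological comparisons; this is valid, but Holm's step-down gives the same familywise error, is never less powerful, and gains when several effects are real

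*Protocol article*

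**What the plan says.** Protocol article, section 4.7.4, on the psychological outcomes: "The level of significance will be α = 0.05, two-tailed, using Bonferroni adjustment for multiple comparisons". The same paragraph says that intervention, time and interaction effects "will be tested using a 2 × 3 two-way repeated measures ANOVA design (group x time"). Table 2 lists the outcomes analysed this way as "Self-efficacy, craving, psychiatric scores" and assigns them to SPSS. The article does not say which tests form the Bonferroni family: scales, time points, post-hoc contrasts, or a combination.

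Section 4.7.1 sizes the trial without any division of alpha. The calculation is for "one interaction between group (2 groups) and assessments (2 repeated measurements"), "set rather conservatively for a medium effect size (Cohen’s F = 0.25), a statistical Power (1-β) of 0.9, a α of 0.05", with "an intra-correlation coefficient of 0.5 and nonsphericity correction of 1".

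Section 2.1.1 expects several psychological outcomes to improve at once: emotions, emotional stability, symptom burden, self-efficacy and craving. Omics variables have a separate rule (false discovery rate, section 4.7.3) and are not affected by this point.

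**The concern.** Single-step Bonferroni compares every p-value with alpha/m. Holm compares the smallest with alpha/m, the next with alpha/(m − 1), and so on, stopping at the first failure. Both control the familywise error at alpha under any dependence between the tests. When several hypotheses are false, Bonferroni keeps charging the full price for hypotheses that have already been rejected.

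At stake is the power of the second and later findings among the psychological outcomes. The trial's hypotheses expect several such findings, and the sample size does not budget for a correction.

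**Working it through.** **1. The plan's own figure.** The plan reports "resulting in a minimum sample size of 46 subjects per group, and a critical F = 4.06". For the group-by-time interaction, λ = f² × N × k / (1 − ρ), with k = 2 assessments, df1 = 1 and df2 = N − 2. With f = 0.25 and ρ = 0.5, λ = 0.0625 × N × 2 / 0.5 = 0.25 N.
- N = 44 in total: power 0.8997.
- N = 46 in total: critical F(1,44) = 4.06, power 0.912.
- N = 92 (46 per group): critical F = 3.95, power 0.997.

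The stated inputs and critical F therefore belong to 46 in total, not 46 per group. That is a separate matter. Here it means that the planned N is generous for the sizing effect.

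**2. Evaluable number.** "Adjusting for expected attrition of about 10%, a total sample size of size of 100 is set". 100 × 0.90 = 90, or 45 per arm.

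**3. Why Holm is never worse.** Every Holm threshold is at least alpha/m. If a p-value is at or below alpha/m, so are all smaller ones, so Holm reaches it and rejects it. The first step is the same in both methods, so the chance of at least one rejection is identical. An illustration with m = 3 and made-up p-values 0.010, 0.020 and 0.040: Bonferroni uses 0.05/3 = 0.0167 throughout and rejects one; Holm uses 0.0167, 0.025 and 0.05 and rejects all three.

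**4. Effect sizes.** A two-arm comparison of change with 45 per arm has noncentrality d / √(2/45) = d / 0.211.
- Sizing effect: √(0.25 × 90) = √22.5 = 4.74, so d = 4.74 × 0.211 = 1.00.
- Pilot self-efficacy: section 4.7.1 gives d ≈ 0.70, so 0.70 / 0.211 = 3.32.
- Pilot F(1,53) = 5.86 (section 1.6), assuming equal arms: d = 2 × √(5.86/55) = 0.65. The value 0.66 used below is an assumption close to this.

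**5. Simulated power, Bonferroni against Holm.** Two-sided t-tests, 45 per arm, correlation between outcomes assumed to be 0.4, each test treated as a one-degree-of-freedom contrast:

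| Setting | Per test | All real effects found |
|---|---|---|
| 3 outcomes, 3 real, d = 0.70 | 0.81 → 0.88 | 0.60 → 0.77 |
| 5 outcomes, 5 real, d = 0.66 | 0.69 → 0.80 | 0.31 → 0.59 |
| 5 outcomes, 3 real, d = 0.66 | 0.69 → 0.73 | 0.43 → 0.52 |

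With normal statistics and an assumed correlation of 0.3:

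| Setting | Per test | All real effects found |
|---|---|---|
| 3 outcomes, 3 real, noncentrality 4.74 (sizing effect) | 0.990 → 0.997 | 0.972 → 0.992 |
| 3 outcomes, 1 real, noncentrality 4.74 | 0.990 → 0.991 | same |
| 3 outcomes, 1 real, noncentrality 3.24 (d ≈ 0.68) | 0.801 → 0.802 | same |

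No simulated data set had a Bonferroni rejection that Holm missed. Holm's familywise error was about 0.04 in the mixed settings at correlation 0.4, and about 0.05 at most elsewhere.

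**6. Sensitivity to correlation.** With five real effects at noncentrality 3.13 (d = 0.66), the per-test gain is 0.119, 0.099 and 0.076 at correlations of 0, 0.4 and 0.8. The gain comes from several effects being real, and correlation reduces it.

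**7. Bonferroni at the sizing effect.** With 90 completers, power is 0.988 for m = 3, 0.978 for m = 6 and 0.966 for m = 10, and stays at or above 0.90 up to m = 54.

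**The case against.** The strongest reply is that nothing is wrong: Bonferroni is a standard, valid procedure and nothing in the article contradicts it. That stands, and the point is put as an improvement only.

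Second, the phrase follows the ANOVA description directly, so it may mean only post-hoc contrasts within one model, and an analysis plan not shown may define the family. This also stands. It leaves the size of the gain open but not its direction, since Holm is never worse for any family.

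Third, at the sizing effect the gain is negligible. That is correct, but that effect corresponds to d = 1.00 on change, above the pilot's 0.70. At the pilot's value the gain is material if several effects are real.

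Fourth, Bonferroni has simple simultaneous confidence intervals that match its tests, and Holm does not readily give these. True, although section 4.7.4 promises no such intervals.

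A reader might infer more: that Holm wins for every family, that Bonferroni throws power away for nothing, or that power after correction limits this trial. The documents do not support these. There is no gain with one test, almost none with one real effect, and none in the chance of at least one rejection. Bonferroni's simpler intervals are a real return. On the plan's own inputs, corrected power stays above the 90% target for any plausible family. The all-five figures are also Holm's best case, and the protocol nowhere requires every scale to succeed.

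**Conclusion.** The point holds as a cheap improvement, not as an error. Holm keeps the guarantee that section 4.7.4 seeks and can only add rejections. The per-test gain is about 7 points (0.81 to 0.88) for three outcomes all at the pilot's effect, about 4 points for five outcomes with three real at d = 0.66, under 1 point at the sizing effect with three outcomes, and essentially zero with one real effect or m = 1. These sizes rest on 45 evaluable per arm, an assumed correlation of 0.3 to 0.4, and assumed families of three or five tests. That Holm is never less powerful rests on none of these.

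**What to change.** Before analysis, change the adjustment named in section 4.7.4 from Bonferroni to Holm step-down, applied to the same family and computed with p.adjust in R, which the plan already uses. Keep Bonferroni only for simultaneous confidence intervals, if any are reported.

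Cost: one phrase and one line of code. The p-values that Table 2 assigns to SPSS must be carried into R for adjustment, and intervals that match the Holm tests are less simple to construct. Sample size and data collection do not change.

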#### Gut microbial domain

2.1.3

In line with previous studies, we hypothesize that smoking contributes to gut microbial imbalances, reduced general bacterial diversity and abundance of commensals, and growth of pathogens (91). We hypothesize that reversed effects in these imbalances will be observable after smoking cessation. Further emphasis will be put on the identification of microbial markers corresponding with general substance craving, history of smoking and success of smoking cessation. Gut microbial correlates of primary emotions and psychiatric symptoms will be identified in exploratory analyses. Analyses will further focus on bacterial genera with a known role (as derived from literature) in the metabolism of SCFA, PUFA, bile acids, and tryptophan (metabolites) (20). Combined metabolome-microbiome analyses will ascertain associations between bacterial abundances and concentrations of relevant metabolites.

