
For beta diversity, db-RDA will be performed on Bray-Curtis, Jaccard, and UniFrac distance matrices (weighted and unweighted) to compare the structural similarities between groups’ microbiomes. Beta diversity indices will be visualized with PCoA plots using Bray-Curtis and Jaccard dissimilarities. The Firmicutes/Bacteroidetes (F/B) ratio will be calculated from the rarefied feature table. Using this, MaAsLin2 will be used to detect differentially abundant taxa and further test associations with variables of interest such as cigarettes per day or metabolic markers (126). Identifications of microbial biomarkers will then be done applying LeFSe both in longitudinal and cross-sectional comparisons. This will be furthered to detect significant differences between groups in the microbial taxonomic abundance using the Analysis of Composition of Microbiomes’ ANCOM-BC implemented within QIIME2 (119).

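### Table 2 lists ANOSIM, which 4.7.5 never describes and which cannot separate a shift in microbial composition from a difference in scatter between the arms

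*Protocol article*

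**What the plan says.** Table 2, printed in section 4.7.4 of the protocol article, summarises the methods for each outcome. Its bacterial-diversity row reads "Kruskal-Wallis, ANOSIM, db-RDA". The cell names no contrast, time point or distance for ANOSIM.

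The text that describes the microbiome analyses does not use ANOSIM. Section 4.7.5 assigns Kruskal-Wallis to alpha diversity. For beta diversity it says "db-RDA will be performed on Bray-Curtis, Jaccard, and UniFrac distance matrices (weighted and unweighted) to compare the structural similarities between" the groups' microbiomes, with PCoA plots as display. Section 4.7.2 plans partial db-RDA and/or PERMANOVA to divide the variance between group, nutrition and control variables. Section 4.7.3 uses ANCOM-BC for the arm comparison of abundance and composition.

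The hypothesis behind these comparisons is in 2.1.3. After describing smoking-related imbalances in the gut flora, it says: "We hypothesize that reversed effects in these imbalances will be observable after smoking cessation". That is a statement about the direction in which composition moves.

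**The concern.** The stated purpose of the beta-diversity comparison is "to compare the structural similarities between groups’ microbiomes", in support of a hypothesis about a shift in composition. ANOSIM ranks all pairwise distances, compares the mean rank between arms with the mean rank within arms, and permutes the arm labels. Permutation is valid only if samples are exchangeable under the null, which requires equal scatter as well as equal average composition.

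Equal arm sizes do not remove the problem. Suppose the arms share a mean and one is looser. Between-arm distances then exceed the tight arm's within-arm distances more reliably than the loose arm's within-arm distances exceed the between-arm ones, because the loose arm's distances also vary more. The statistic drifts above zero with no shift at all.

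At stake is how a result is described. A significant ANOSIM could be reported as a change in community structure in the hypothesised direction when the data show only that one arm is more heterogeneous.

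**Working it through.** **Inputs.** Arm sizes are 50 and 50 (Table 1). The minimum of 46 per group in 4.7.1 was also run. A nominal 5% level is assumed: 4.7.4 says "The level of significance will be α = 0.05, two-tailed, using Bonferroni adjustment for multiple comparisons", but for the psychological analyses, and 4.7.3 plans false-discovery-rate control for the omics data. The ratio of spread between arms is not in the document; 1.0 to 1.5 is assumed. One sample per participant is assumed. The plan contains no ANOSIM figure to reproduce.

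**Statistics.** ANOSIM R = (mean between-arm rank − mean within-arm rank) / (M/2). With 100 samples M = 100 × 99 / 2 = 4,950 distances, of which 50 × 50 = 2,500 are between arms and 2 × (50 × 49 / 2) = 2,450 within. The comparator is the PERMANOVA (one-factor db-RDA) pseudo-F = (SST − SSW) / [SSW / (n − 2)], with n − 2 = 98.

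**Main simulation.** 400 data sets per setting, 199 permutations each, Monte Carlo standard error at most 2.5 points. The arms have identical mean composition and differ only in spread. Entries are the percentage rejecting at 5%, with 50 per arm unless stated.

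| SD ratio | 1.0 | 1.1 | 1.2 | 1.3 | 1.5 |
|---|---|---|---|---|---|
| ANOSIM, Gaussian, 20 dimensions | 4 | 15 | 66 | 99 | 100 |
| PERMANOVA, same data | 4 | 6 | 4 | 5 | 5 |
| ANOSIM, Bray-Curtis, 60-taxon Dirichlet-multinomial | 5 | 11 | 47 | 88 | 100 |
| PERMANOVA, same data | 6 | 7 | 16 | 36 | 97 |
| ANOSIM, Gaussian, 46 per arm | 6 | 14 | 63 | 97 | 100 |

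In the Bray-Curtis rows a ratio of 1.2 corresponds to mean within-arm distances of 0.533 and 0.477, that is 0.533 / 0.477 = 1.12.

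**Other settings.**
- Euclidean, 50 dimensions, 45 per arm: 23% at a ratio of 1.1 and 88% at 1.2. A further Euclidean run at 50 per arm gave 28% and 91%, against 7% and 5% for PERMANOVA.
- Dirichlet, 50 per arm, precision 30 against 40 (SD ratio √(41/31) = 1.15): ANOSIM 27%, PERMANOVA 8%. Precision 25 against 40 (√(41/26) = 1.26): 86% and 19%.
- Low dimensions: at 1.2, ANOSIM rejects 13% (2 dimensions) and 27% (5 dimensions); at 1.3, 30% and 60%.
- Unequal arms, ratio 1.2, 20 dimensions: about 100% if the more scattered arm has 40 and the other 50; 0% if the more scattered arm has 50 and the other 40.

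**Does a mix of responders create this?** With 45 per arm, 50 dimensions, and 30% or 50% of one arm shifted 1 to 4 SD in a common direction, the spread ratio is only 1.00 to 1.04. With 50% shifted by 2 SD, ANOSIM rejects 62% and PERMANOVA 66%, both because the mean really moved. A 10% excess in spread needed a shift of 6.5 SD, where both reject 100%.

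**The case against.** The strongest reply is that ANOSIM carries no stated inference. It is one word in a summary table, and sections 4.7.2, 4.7.3 and 4.7.5 give the arm comparison to db-RDA/PERMANOVA and ANCOM-BC. This stands. A reader might infer that the trial will declare a compositional difference from ANOSIM; no passage says so.

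Second, the arms are randomised. If the programme does nothing to the microbiome, the arms are exchangeable and ANOSIM holds its level (about 4% to 6% at 46 or 50 per arm). This also stands: a rejection caused by spread misdescribes an effect and is not a false claim that one exists.

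Third, a reader might expect unequal spread because the intervention arm will contain people who quit, cut down and continue. A shift in a common direction among some participants hardly changes the spread and makes both tests reject at similar rates. Extra scatter without a mean shift needs responses that differ in direction. That is possible, but the document does not make it likely.

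Fourth, a reader might hold that ANOSIM breaches 4.7.3 because it takes no covariates. That section enters covariates in MOFA and ANCOM-BC; it does not require them in every listed test.

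Finally, a dispersion test is the kind of detail an analysis plan would hold, and section 2 calls the work largely exploratory. Its absence from the article is therefore not the fault. The fault is a named method that does not fit the question and a table that disagrees with the text.

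**Conclusion.** The point holds as a minor, inexpensive improvement. Table 2 names a test that section 4.7.5 does not describe and that cannot tell a change in location from a change in spread. With equal mean composition and about 50 per arm, its rejection rate at a nominal 5% is roughly 11% to 28% at 10% more spread and 47% to just over 90% at 20%. In 2 to 5 dimensions a 20% excess gives only 13% to 27%.

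These figures depend on assumed spread ratios and data models. They show what the test responds to and do not predict this trial's result. A significant ANOSIM on its own should not be read as the reversal hypothesised in 2.1.3. The planned db-RDA/PERMANOVA is clearly better, but under Bray-Curtis it also exceeds its level when spread differs, so dispersion needs to be examined beside it.

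**What to change.** 1. Delete ANOSIM from the bacterial-diversity row of Table 2, so that the table agrees with 4.7.5.
2. Base the beta-diversity contrast between arms on the db-RDA/PERMANOVA already planned.
3. Report a test of homogeneity of multivariate dispersion on the same distance matrices, next to the planned PCoA plots.
4. Where dispersion differs between arms, describe a significant arm result as a possible difference in variability, not as an established shift in composition.

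The cost is one table entry and one extra test on distance matrices that will exist anyway. No planned analysis capability is lost. The downside is more cautious wording of some significant results.
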